#### Secondary outcomes:

Feasibility of using a pulse oximeter as part of iCCM; accuracy of pulse oximetry when used by CLHWs against a standardized measurement by a trained supervisor; and impact of pulse oximetry on referral and treatment outcomes i.e., does it increase safety of iCCM and improve referrals?

### Study procedures

#### Screening and enrolment

Children aged 2–59 months presenting to a CLHW with cough and/or difficult breathing will be evaluated using eligibility criteria for enrolment (Figure 1). As the CLHWs in Bangladesh and Ethiopia are based at a small health facility and cover a larger population and geographical area compared to the CLHWs in India and Malawi who are based at community level, community volunteers in Bangladesh and Ethiopia will be trained to make home visits to help identify sick children and link them to the CLHWs.

In the intervention group, the CLHWs will take a detailed patient history, perform clinical examination and record the findings on a standardized case recording form (CRF). The CLHWs will also perform pulse oximetry on all children with chest indrawing to identify hypoxaemia (SpO_2_ <90% by pulse oximetry). Children having any danger sign or hypoxaemia, or whose mothers/caregivers don’t consent to participate in the study will be referred to a referral level health facility after the first dose of amoxicillin. Parents/caregivers of these children will be requested to give consent for follow-up by an IOA on days 6 and 14. In the control group, these children will be referred to a referral level health facility. A detailed patient history and clinical examination will be performed by the CLHW, and findings will be recorded on a standardized CRF.

All children meeting the eligibility criteria will be examined by a study supervisor to validate the CLHW’s findings in both intervention and control groups. Those fulfilling the eligibility criteria will be enrolled after a written informed consent is obtained from the mother or caregiver. Screening, clinical assessment, enrolment and provision of study medication will take place within one hour of identifying the case. Details of the implementation strategy at various sites are summarized in Table 3.

### Randomization, allocation and masking

The cluster or unit of randomization is Union in Bangladesh, Health Sub-center in India, and Health Center in Ethiopia and Malawi. Stratified randomization has been carried out based on the population of the clusters i.e., clusters divided into two stratums, median or above and below the median. Randomization list has been prepared by a WHO staff not involved with the site work. For Bangladesh, 52 clusters (26 in intervention and 26 in control), in Ethiopia 20 clusters (10 in intervention and 10 in control), in India 92 clusters (46 in intervention and 46 in control) and in Malawi, 44 clusters (22 in intervention and 22 in control) were selected. Masking of participant and study team is not possible due to nature of the intervention. However, attempts will be made to keep the outcome assessors unaware of group allocation.

### Use of pulse oximetry

Hypoxaemia is a major contributor to mortality and a major complication of pneumonia,^20–23^ but is difficult to identify clinically. Supplemental oxygen needed for management of hypoxaemic children is neither consistently available in low- and middle-income countries nor always appropriately used.^23–26^ Using non-invasive pulse oximetry technology, hypoxaemic children at a higher risk of poor outcomes can be identified and promptly referred to a health facility that has oxygen. Current iCCM tool does not identify hypoxaemic children. CLHWs will be trained to use pulse oximetry in the intervention group. This will increase the safety of study participants and improve referrals. *Masimo* RAD-5v handheld portable pulse oximeters will be provided to CLHWs, study supervisors and independent outcome assessors in intervention clusters, but only to study supervisors and independent outcome assessors in the control group. They will be trained to use and maintain them.

### Follow-up and assessment of adherence to treatment

In the intervention group, CLHWs will follow all enrolled children on days 2, 4 and 7. The mothers/caregivers will be advised to return to the community clinic in Bangladesh, health post in Ethiopia, and to a CLHW in India and Malawi for scheduled follow-ups. Mothers/caregivers will be explained all danger signs and counseled on when to contact CLHWs any time between the scheduled follow-up visits. CLHW will visit a child at home who does not come for follow-up.

During the follow-up visits, CLHWs will evaluate the child for clinical signs. If any danger sign or deterioration is observed, the CLHW will call the study supervisor to physically confirm the findings and refer the child to a higher-level health facility as per iCCM protocol. CLHWs will check for presence of adverse drug reactions during follow up visits. They will count the remaining tablets to assess adherence. In instances when follow-up visit is scheduled after the completion of treatment or the parents/caregivers lose/misplace the remaining medicine, caregiver will be asked about the frequency of administration and the number of tablets used. An enrolled child will be considered adherent if s/he has received either all oral amoxicillin doses for five days or at least 8 doses (80%). Adherence to treatment provided to the children in the control group will also be assessed in the same manner.

The mobile phone numbers of the CLHWs and study supervisors will be shared with mothers/caregivers to contact them if any adverse event occurs between the follow-up visits.

### Outcome ascertainment

IOA will visit enrollees in both groups on days 6 and 14 of enrolment, at home or in hospital, to assess outcomes. The IOA will clinically examine the child and perform pulse oximetry.

### Separation between the outcome assessment and treatment teams

The proposed trial cannot be blinded due to the nature of the treatment, so we have incorporated independent outcome assessment to reduce potential measurement bias. We will hire trained nurses, physicians or clinical field workers as IOA who will be independent of the enrolment and treatment to evaluate study outcomes. IOAs will be trained specifically for research purposes in the standard iCCM, enhanced iCCM and study procedures.

### Demand generation activities

Families will be encouraged to seek care from CLHWs for their sick children through extensive advocacy and information, education, and communication (IEC) activities. In the intervention group, IEC activities will aim to create awareness about the CLHWs’ new role to provide treatment for chest indrawing pneumonia. In the control group, the IEC activities will focus on sustaining the community’s demand for standard iCCM treatments provided by CLHWs. The methods will include posters with pictures and simple messages in local languages, and audio announcements. Posters and wall paintings will be placed at high-visibility public places i.e., government buildings, marketplaces and village meeting venue.. The local CLHW’s name and phone number will be pasted outside each CLHW’s home in India and Malawi so that the community can contact them easily. Periodic loudspeaker announcements will be made across the study areas. Governments use these methods to promote new programmes.

Members of existing community support groups will be sensitized about the signs of illness in children to disseminate them. Parents or caregivers will be shown video clips on chest indrawing at immunization centers and mothers’ gatherings at primary schools. Pictorial leaflets will be distributed, and discussion sessions will be held in schools on pneumonia features.

### Quality control and assurance

#### Training and standardization of CLHWS and study teams

The training of CLHWs, study supervisors, IOAs, study coordinators and investigators will be a two-step process. WHO experts will facilitate a six day training course for master trainers which, will be organized for selected senior level participants at one of the sites using the study standard operating procedures, and the WHO modules on “Caring for the Sick Child in the Community module” and pulse oximetry.^27^ These master trainers will then train the other study staff at their respective sites. For the intervention group the iCCM chart booklet and other training materials will be adapted to include enhanced components of iCCM. CLHWs will be trained to identify lower chest indrawing in children below 5 years, to recognize and record danger signs of illness as described in the WHO-UNICEF training package for CLHWs, and refer or take any child with a danger sign to a health facility.^27^ All CLHWs, study supervisors, IOAs, and study coordinators will be trained in study objectives and strategy, and iCCM modules.

The CLHWs training materials will be translated into respective local languages. Government trainers will be involved in the training of the CLHWs. The CLHWs and supervisors of intervention clusters and IOAs will be trained in enhanced iCCM, whereas the CLHWs and supervisors from control clusters will be trained in standard iCCM. The training modules will include 6-day scheduled classroom and clinical training sessions. All CLHWs will be evaluated post training and those found weak will be retrained.

Additionally, all study staff will be trained in Good Clinical Practices (GCP). The study sites will also develop a system of periodic refresher training of CLHWs, supervisors and IOAs through video demonstration and/or clinical practice including pulse oximetry.

Standardization of measurement of respiratory rate, pulse oximetry, body temperature, MUAC and identification of danger signs will be done periodically (at least once every six months) for all CLHWs, supervisors and IOAs. The study physicians at every site will conduct these standardizations.

#### Study oversight, supervision and monitoring

A study supervisor will independently validate all children assessed as potential enrollees by a CLHW in both intervention and control groups. Supervisors will confirm pulse oximetry findings by CLHWs in the intervention group. A proportion of the follow-up visits will be accompanied by the supervisors, who will also conduct independent unaccompanied visits. Principal and co-investigators, study coordinators, and managers will also visit study sites to review project quality and cross-check a small proportion of collected CRFs and provide feedback as required.

Periodic meetings will be held to review research team performance, enrolment progress, field visit observations, address problems and identify solutions. Government managers at district/sub-district level will be involved in supervision and monitoring activities.

### External monitoring

WHO study coordinating team will visit each site prior to initiation of implementation to assist in preparation and planning. All sites will submit monthly progress report to WHO. WHO monitors will visit each site periodically to assess progress, compliance with study protocols, quality and accuracy of data collected, quality of care and child safety. In those visits a proportion of completed CRFs and all serious adverse event (SAE) reporting forms will be reviewed. Recommendations from the monitoring visits observations will be discussed with the research teams and follow up actions will be undertaken.

Data-based monitoring will be carried out by the central data coordination centre (DCC) in collaboration with the WHO study coordinator.

### Logistics and commodities

Trained CLHWs will be equipped with necessary medicines, equipment and logistics for pneumonia case management such as oral amoxicillin, pulse oximeter, thermometer, weighing scale, respiratory rate counting timer, MUAC tape, CRFs and other necessary materials. The study teams will monitor the CLHW’s equipment for periodic standardization and replacement of faulty devices, if any. The consumables will be replenished as required.

### Data collection instruments and procedures

CLHWs, study supervisors and IOAs will collect data. The supervisor will complete a confirmation form for each case before enrolment. A follow-up form (only in the intervention group) and pulse oximeter use checklist will also be completed for each case separately by the CLHWs and supervisors. The IOAs will complete an outcome assessment form on days 6 and 14 for both intervention and control groups. IOAs will fill a separate form describing for SAE. Completed forms will be reviewed by supervisors for completeness and corrected before data entry. Supervisors and IOAs will submit CRFs to the study site office. A coordinator/co-investigator will check the CRF to evaluate their completeness. Queries will be sent back to the field before CRFs are transferred to the data entry teams.

### Data management

The data management team at each site will be responsible for the site’s day-to-day data management activities. The DCC, an independent institution will coordinate all study data. DCC will develop a common database capable of keeping automated record of all changes, will be used by all sites. A DCC team will help to set up data management systems at all sites and train the local data managers and data entry operators. All sites will be periodically upload data at the central DCC server after application of range and across form consistency checks. DCC will run checks on uploaded data and the queries will be sent to the site-specific data managers for resolution. After resolution of these queries, the clean database will be uploaded to the DCC server site.

### Data analysis

The primary analysis will be a per-protocol combined analysis across all the sites. Simple comparisons of means and proportions by treatment groups will be used to check whether the randomization scheme resulted in baseline comparability. The analyses will compare non-inferiority between the standard iCCM and the enhanced iCCM. The comparison of proportions of children with treatment failure in each treatment group and the difference in the risk of treatment failure together with 95% confidence interval will be calculated. Data adjusted for any covariates which may be unbalanced at baseline and likely to influence the primary outcomes. Those who will be lost to follow-up or withdraw consent after enrolment will not be included in the analysis. An intention-to-treat analysis will also be conducted. Secondary analyses will be performed to investigate the secondary outcomes. Additionally, univariate and multi-variate regression analyses will be performed to identify predictors of treatment failure.

Separate data analysis workshops will be undertaken at the end of in the study for Asian and African sites. Data cleaning for the analysis of all the primary and secondary outcomes will be completed before the workshops and the databases will be locked.

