## INTRODUCTION

Of an estimated 0.8 million pneumonia deaths in children under-five years, majority occur in sub-Saharan Africa and South Asia.^1^ Progress in these regions is slow and the disparity between Africa and the rest of the world has grown.^2,3^ As many as 138 million pneumonia episodes are estimated to occur every year.^4^ Mortality among children with pneumonia varies between 0.1% and 30%, depending upon age, severity of signs, promptness and appropriateness of treatment.^5–8^

The World Health Organization (WHO)/UNICEF integrated Community Case Management (iCCM) protocol recommends that community level health workers (CLHWs) refer all children under five years of age with lower chest indrawing to a referral health facility/hospital.^9^ However, many families do not accept referral advice for a variety of reasons, thus reducing access to treatment.^3,10,11^ Several studies reported effectiveness of oral amoxicillin for chest indrawing pneumonia in 2–59 months old children.^12–16^ WHO revised pneumonia treatment guidelines recommending oral amoxicillin for treatment of chest indrawing pneumonia in 2–59 months old children by trained health workers on outpatient basis.^17^ The 2014 Integrated Management of Childhood Illness (IMCI) chart booklet for health facilities is based on this recommendation, which was not extended to the iCCM protocol for community because of insufficient safety and efficacy evidence.^18^

Access to pneumonia treatment could increase substantially if evidence were generated to show effectiveness and safety of oral amoxicillin for chest indrawing pneumonia in 2–59 months old children treated by CLHWs at community level. Additionally, it could decrease referrals, thereby reducing the load on overburdened hospitals and diminishing treatment costs. The overall goal of this study is to contribute to the evidence base for potential revision of the iCCM protocol and its harmonisation with the IMCI protocol.

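### The per-protocol analysis alone decides non-inferiority, while the article's only adherence rule can exclude early failures and has no consistent procedure in the control group

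*Protocol article*

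**What the plan says.** **Analysis sets (Data analysis).** "The primary analysis will be a per-protocol combined analysis across all the sites". The only exclusion named there is: "Those who will be lost to follow-up or withdraw consent after enrolment will not be included in the analysis". The section adds: "An intention-to-treat analysis will also be conducted". It does not say what follows if the two analyses disagree.

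**Adherence (Follow-up and assessment of adherence to treatment).** The single rule is: "An enrolled child will be considered adherent if s/he has received either all oral amoxicillin doses for five days or at least 8 doses (80" per cent). It is judged by tablet count, or by caregiver report when tablets cannot be counted, at the follow-up visits of the community level health worker (CLHW). For the other arm the section says: "Adherence to treatment provided to the children in the control group will also be assessed in the same manner".

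**Control procedures.** Data collection instruments and procedures lists "A follow-up form (only in the intervention group) and pulse oximeter use checklist". Table 3 enters NA for follow-up and for supervision in the control clusters. Control children receive a first dose and are then referred. The Introduction says that "many families do not accept referral advice for a variety of reasons".

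**Outcome (Study outcomes).** Failure includes death on days 1 to 14 and serious reactions to amoxicillin on days 1 to 5. Persistent chest indrawing, and hospitalization or an indication for it, are judged on day 6.

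**The concern.** A per-protocol set is selected on what happens after enrolment. If the selection depends on the outcome, or is measured differently in the two arms, the groups compared are no longer the randomised ones.

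Both risks are present. The dose rule counts doses received and does not ask why a course stopped. A child who dies on day 3, or who has a serious reaction and stops, cannot reach eight doses and would be labelled non-adherent because of the failure. In the control arm the rule counts doses of a drug for which the CLHW gives only the first dose, at visits that Table 3 says do not occur. Declining referral is also part of how standard iCCM works in practice, so excluding those families would change the comparator.

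The result is meant to inform revision of the iCCM protocol. The set that decides non-inferiority should not be open to either problem.

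**Working it through.** **1. Which failures are exposed.** Two doses a day for five days is 10 doses (Study intervention), so dose 8 falls at about the end of day 4. Death, a serious reaction, or a change of treatment in a child who also meets the failure definition can come before that. Chest indrawing still present on day 6 does not by itself prevent eight doses. Only part of the failures is therefore exposed, and the article does not give the share.

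**2. The sections on control adherence, side by side.**
- Adherence section: assessed in control as in intervention, that is, by tablet count or caregiver report at CLHW visits.
- Data collection section: follow-up form in the intervention group only.
- Table 3: control follow-up NA; first dose, then referral.
- Outcome ascertainment: the independent outcome assessor (IOA) visits both groups on days 6 and 14. No adherence task is assigned to those visits.

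As written, these do not give one procedure for both arms.

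**3. The planned sample size reproduces.** Inputs from the Sample size section: 10% failure in each group, margin 5 points, one-sided 2.5%, 90% power, design effect 1.6, attrition 10%.

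n = (1.960 + 1.282)² × (0.10×0.90 + 0.10×0.90) / 0.05² = 756.5

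756.5 × 1.6 = 1210.5. Dividing by 0.9 gives 1345; multiplying by 1.1 gives 1332. The stated 1340 lies between. Evaluable children: 1340 × 0.9 = 1206 per group.

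**4. Chance of declaring non-inferiority.** With failure proportions p1 (intervention) and p0 (control) in the analysed set:

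SE = √{1.6 × [p1(1−p1)/n1 + p0(1−p0)/n0]}

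P = Φ{(0.05 − (p1 − p0))/SE − 1.96}

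With nothing dropped, 10% v 10% gives P = 89.9% (the planned power). The boundary case, 15% v 10%, gives P = 2.5%.

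**5. Early failures lost in the intervention arm only** (truth 15% v 10%). The lost share d of all intervention children is my assumption. p1 = (0.15 − d)/(1 − d), n1 = 1206(1 − d).

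| d | share of intervention failures (d/0.15) | p1 | difference, points | false non-inferiority |
|---|---|---|---|---|
| 0 | 0 | 15.0% | 5.0 | 2.5% |
| 1% | 7% | 14.1% | 4.1 | 7.4% |
| 2% | 13% | 13.3% | 3.3 | 18.0% |
| 3% | 20% | 12.4% | 2.4 | 36.2% |

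**6. Failures lost in both arms.** A share f of failures is dropped, so p becomes p(1 − f)/(1 − pf).

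| f intervention | f control | difference, points | false non-inferiority |
|---|---|---|---|
| 10% | 10% | 4.6 | 4.2% |
| 20% | 20% | 4.2 | 7.2% |
| 10% | 20% | 5.5 | 1.1% |
| 10% | 30% | 6.5 | 0.2% |

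**7. Control children excluded for declining referral.** Assume 40% of control is excluded and the excluded children fail at rate q, so p0 among those kept is (0.10 − 0.4q)/0.6, with n0 = 0.6 × 1206. Combined with d = 1%, 2%, 3% in the intervention arm:
- q = 10% (p0 = 10%): 7%, 15%, 29%.
- q = 12% (p0 = 8.7%): 1.3%, 4.1%, 10.8%.
- q = 15% (p0 = 6.7%): below 1% throughout.

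The sign turns on quantities that the documents do not give.

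**The case against.** **The rule is not tied to the set.** No sentence makes the eight-dose rule the definition of the per-protocol set, and the analysis section names only loss to follow-up and withdrawal. The full protocol or SAP may define the set properly, and its absence from an article is no fault. This stands, so the point is conditional. It still matters because a per-protocol set normally needs some adherence criterion to differ from intention-to-treat, and this is the only one given.

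**Few failures are exposed.** This also stands. The assumed 1% to 3% of children amount to 7% to 20% of all intervention failures, and nothing in the article supports a particular share.

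**Stronger readings that a reader might infer.**
- That the bias must favour non-inferiority. It does when losses fall mainly on the intervention arm or equally on both. It reverses when failures are lost more heavily in control.
- That the rule cannot be applied in control at all. The article says adherence will be assessed there, allows caregiver report, and has IOA visits in both arms. What is missing is a consistent procedure.
- That excluding control children would leave the trial short of power. The Randomization section lists 52 + 20 + 92 + 44 = 208 clusters against the 90 required. At 30 cases per cluster and 10% attrition that is 104 × 30 × 0.9 = 2808 per group. Even with 40% of control excluded (1685 left), power at 10% v 10% is about 99%.

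**Intention-to-treat is planned.** It is a partial safeguard, but the article attaches no decision to it.

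**Conclusion.** The point holds in a limited form, as an inexpensive improvement. Three things are on the page: per-protocol alone is primary; the only adherence rule has no exception for death or failure before dose 8; and the statements on control adherence conflict. That early failures would actually be dropped is conditional on the rule defining the set.

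If it does, the false non-inferiority rate at the margin could rise from 2.5% to about 7%, 18% or 36% with intervention-only losses of 1%, 2% or 3% of children. It would be about 4% or 7% if 10% or 20% of failures are lost equally in both arms, and could fall to about 1% or lower if control loses more. These figures assume true failure of 15% v 10%, 1206 evaluable per group, design effect 1.6 and a normal approximation; the loss shares are assumptions. The documents do not settle the direction, which is itself a reason not to let this set decide alone.

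**What to change.** 1. Declare non-inferiority only if the upper 95% limit is below 5 points in both the intention-to-treat set (all enrolled children, as allocated) and the per-protocol set.
2. State what defines the per-protocol set. Children who die or meet treatment failure before dose 8 stay in it as failures, with adherence judged on the doses due before that event.
3. Define control adherence on the control strategy: whether the referral was attended and the treatment prescribed there was taken.
4. Collect adherence in both arms at the existing day 6 IOA visit.
5. Reconcile the adherence section, the data collection section and the control rows of Table 3.

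The cost is some analysis wording, a few questions on the day 6 form, and a claim that is slightly harder to reach. No treatment or clinical procedure changes.

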### Control

In the control group, CLHWs will refer all children with chest indrawing pneumonia to the nearest health facility in Malawi and to a higher level health facility in India, Bangladesh and Ethiopia.

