**Characteristics of clusters**				
Name	Union	Health sub-centers	Health center	Health center
Median population	25492	10318	25492	20926

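### Adjustment covariates are to be chosen after comparing the arms at baseline; with children enrolled after open cluster allocation, they should be fixed in advance

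*Protocol article*

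**What the plan says.** All references are to the protocol article; no SAP is shown.

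- **Data analysis** defines the primary analysis: "The primary analysis will be a per-protocol combined analysis across all the sites". The measure is a risk difference: "the difference in the risk of treatment failure together with 95% confidence interval will be calculated".
- The same section plans a baseline check: "Simple comparisons of means and proportions by treatment groups will be used to check whether the randomization scheme resulted in baseline comparability". The adjustment rule follows: "Data adjusted for any covariates which may be unbalanced at baseline and likely to influence the primary outcomes". A covariate must therefore meet two conditions: it is unbalanced, and it is likely to be prognostic. The section gives no list and no criterion for either condition. It does not say whether an adjusted result replaces the crude one or stands beside it.
- **Randomization, allocation and masking** reports 1:1 allocation of clusters in each country (52 + 20 + 92 + 44 = 208), stratified by population: "clusters divided into two stratums, median or above and below the median". Participants and study team are unmasked.
- **Screening and enrolment** places identification, confirmation and consent of each child after the cluster's allocation.
- **Demand generation activities** differ by arm. Intervention messages promote the health workers' "new role to provide treatment for chest indrawing pneumonia"; control messages sustain demand for standard iCCM.
- **Use of pulse oximetry** gives oximeters to health workers in intervention clusters only. Supervisors and outcome assessors have them in both arms.

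**The concern.** In an individually randomised, masked trial, baseline imbalance is chance, and adjusting for what looks unbalanced is mainly untidy. Here there is a second source. Clusters are randomised, but children enter later, through staff and families who know the allocation, and under different publicity. A systematic difference in the severity of enrolled children is possible, and repeating the cluster randomisation would not average it away. If milder children entered intervention clusters, the estimate would move towards non-inferiority.

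A rule that reacts to observed imbalance suits this badly. It catches large shifts and misses moderate ones, yet a moderate shift in a prognostic covariate still biases the estimate. It also lets the choice of model follow sight of the data by arm, so one verdict could rest on any of several confidence intervals.

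A smaller, related matter is country and population stratum. They structured the allocation, and country may well be prognostic; for example, control children are referred "to the nearest health facility in Malawi and to a higher level health facility in India, Bangladesh and Ethiopia". The article does not say whether these terms enter the model.

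**Working it through.** **1. The plan's own figure.** Inputs from Sample size: 10% failure in both groups, 5-point margin, 90% power, two-sided 95% interval, design effect 1.6, attrition 10%.
- Per group before inflation: (1.960 + 1.282)² × 2 × 0.10 × 0.90 / 0.05² = 757.
- Times 1.6 = 1211. Dividing by 0.9 gives 1346; multiplying by 1.1 gives 1333. The stated 1340 is reproduced.
- With 30 children per cluster, the implied ICC is 0.6 / 29 = 0.0207.

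**2. What the trigger does under a recruitment shift.** The article gives no figures for this, so the inputs are assumptions. A cluster-level simulation used 208 clusters and 6000 runs, with the true difference set at the 5-point margin. Country failure rates were 5% to 15%, and there were five covariates, each worth 3 points of risk per SD of the cluster mean. One covariate was 0.25 SD lower in the intervention arm. The trigger was p<0.05.

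| Analysis | Bias (points) | Empirical SE | Model SE | False non-inferiority (nominal 2.5%) |
|---|---|---|---|---|
| Unadjusted | -0.77 | 1.59 | 1.71 | 5.0% |
| Strata only | -0.77 | 1.59 | 1.61 | 6.6% |
| Imbalance-triggered, no strata | -0.27 | 1.52 | 1.70 | 2.1% |
| Prespecified covariates and strata | 0.00 | 1.32 | 1.34 | 2.3% |

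The trigger selected the shifted covariate in 44% of runs.

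**3. Check by formula.** With 104 clusters per arm, the SE of the difference in covariate means is √(2/104) = 0.1387 SD. Put μ = shift / 0.1387. The residual shift is the expected difference over the cases not selected:

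0.1387 × [μ(Φ(1.96-μ) - Φ(-1.96-μ)) + φ(-1.96-μ) - φ(1.96-μ)]

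Multiplying by 3 points per SD gives the following range:

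| Shift (SD) | μ | Selected | Unadjusted bias | Residual bias |
|---|---|---|---|---|
| 0.10 | 0.72 | 11% | -0.30 | -0.19 |
| 0.25 | 1.80 | 44% | -0.75 | -0.26 |
| 0.50 | 3.61 | 95% | -1.50 | -0.03 |

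The middle row agrees with the simulation. Bias scales in proportion to the risk per SD, so 1.5 points per SD halves each entry. The trigger deals well with a large shift and poorly with small and moderate ones.

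**4. No recruitment shift.** With each covariate worth 1.5 points per SD and country rates equal or between 5% and 20%, triggered adjustment gave false non-inferiority rates of 1.3% to 2.3%, which is not inflated. Leaving out country and stratum left the estimate unbiased. With unequal country rates the interval was too wide (model SE 1.51 to 1.53 against empirical 1.36 to 1.41) and the error rate was about 1.5%. With equal country rates nothing was lost (2.4%).

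**5. Precision from country and stratum.** Let f be the share of between-cluster variance they explain; the article gives no value. Design effect = 1 + (m - 1) × 0.0207 × (1 - f). The SE ratio is the square root of the ratio of design effects.

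| f | m = 30 | SE falls by | m = 2680/208 = 12.9 | SE falls by |
|---|---|---|---|---|
| 0 | 1.60 | 0 | 1.25 | 0 |
| 0.25 | 1.45 | 5% | 1.18 | 2.5% |
| 0.50 | 1.30 | 10% | 1.12 | 5% |
| 0.75 | 1.15 | 15% | 1.06 | 8% |

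**The case against.** The strongest reply has four parts.

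- **An article condenses a fuller plan, and model terms belong in the SAP.** This stands for country and stratum. A reader might infer from the word combined that the analysis ignores the randomisation strata. The text does not say so; it is silent, and omission would in any case leave the estimate unbiased and the test conservative. The reply does not reach the covariate rule, which the article states outright. An SAP that fixed the covariates in advance would replace that rule.
- **The rule is not driven by imbalance alone.** Correct: a covariate must also be likely to influence the outcome. But nobody has said which covariates those are, so that judgement too is left until the arms have been compared.
- **The shift is conjecture.** Also fair. The article gives no evidence that milder children will enter intervention clusters, and a supervisor examines every eligible child in both arms against common criteria that exclude hypoxaemia. This limits misclassification of eligibility. It does not equalise severity among children who are all eligible.
- **The harm shown is small.** The residual bias is 0.27 points against a margin of 5, and the trigger's error rate in that scenario was 2.1%. This stands as far as it goes. The rate stayed low because the simulated model omitted country and stratum, so its interval was too wide (1.70 against 1.52). Two faults offset each other. The trigger combined with strata was not simulated.

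**Conclusion.** The concern holds for the stated covariate rule. Choosing covariates from between-arm comparisons is a poor method in a cluster trial that enrols after open allocation, and a better one costs almost nothing. The demonstrated effect is partial correction of bias: about a quarter of a point left over at a 0.25 SD shift and 3 points per SD, and between 0.03 and 0.26 points over shifts of 0.10 to 0.50 SD. Inflation of the false non-inferiority rate by the trigger was not shown. The shift, the prognostic strength, the country rates and the p<0.05 criterion are all assumptions.

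On country and stratum the finding is a request for a statement, not an error. The gain in SE is about 5% to 15% at 30 children per cluster, or about 2.5% to 8% if 2680 children are spread over 208 clusters, for assumed shares of 25% to 75%.

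A reader might also take the row "Median population" in Table 1 for the stratum cut-points and, finding it hard to square with Malawi's total, conclude that the strata are wrong. The article does not say that those medians are the cut-points, and the population totals are rounded. The stratum variable would come from the randomisation list, so Table 1 does not affect the analysis.

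**What to change.** 1. Delete the imbalance trigger. Keep the baseline table as description only.
2. Before anyone sees data by arm, fix the primary model as a cluster-adjusted risk difference. Obtain it as a standardised marginal difference that always adjusts for age and the supervisor's enrolment SpO2.
3. Add respiratory rate and temperature if the case record forms capture them at enrolment in both arms. The article does not list the fields of the supervisor's form, so check this first.
4. Use MUAC only with a stated rule for infants under 6 months, because the MUAC criterion applies from 6 months.
5. State that country and population stratum, taken from the randomisation list, enter the primary model. Make this change together with item 2: in the shift scenario, adding strata without the covariates raised the false non-inferiority rate from 5.0% to 6.6%.
6. Report the unadjusted difference beside the primary result, labelled as supportive.

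The cost is a paragraph of analysis text and a check of the forms. No change to sample size, visits or conduct is needed if the named variables are already recorded.
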